## Abstract

**Background:**

Recovery features strongly in Australian mental health policy; however, evidence is limited for the efficacy of recovery-oriented practice at the service level. This paper describes the Principles Unite Local Services Assisting Recovery (PULSAR) Specialist Care trial protocol for a recovery-oriented practice training intervention delivered to specialist mental health services staff. The primary aim is to evaluate whether adult consumers accessing services where staff have received the intervention report superior recovery outcomes compared to adult consumers accessing services where staff have not yet received the intervention. A qualitative sub-study aims to examine staff and consumer views on implementing recovery-oriented practice. A process evaluation sub-study aims to articulate important explanatory variables affecting the interventions rollout and outcomes.

**Methods:**

The mixed methods design incorporates a two-step stepped-wedge cluster randomized controlled trial (cRCT) examining cross-sectional data from three phases, and nested qualitative and process evaluation sub-studies. Participating specialist mental health care services in Melbourne, Victoria are divided into 14 clusters with half randomly allocated to receive the staff training in year one and half in year two. Research participants are consumers aged 18–75 years who attended the cluster within a previous three-month period either at baseline, 12 (step 1) or 24 months (step 2). In the two nested sub-studies, participation extends to cluster staff. The primary outcome is the Questionnaire about the Process of Recovery collected from 756 consumers (252 each at baseline, step 1, step 2). Secondary and other outcomes measuring well-being, service satisfaction and health economic impact are collected from a subset of 252 consumers (63 at baseline; 126 at step 1; 63 at step 2) via interviews. Interview-based longitudinal data are also collected 12 months apart from 88 consumers with a psychotic disorder diagnosis (44 at baseline, step 1; 44 at step 1, step 2). cRCT data will be analyzed using multilevel mixed-effects modelling to account for clustering and some repeated measures, supplemented by thematic analysis of qualitative interview data. The process evaluation will draw on qualitative, quantitative and documentary data.

**Discussion:**

Findings will provide an evidence-base for the continued transformation of Australian mental health service frameworks toward recovery.

**Trial Registration:**

Australian and New Zealand Clinical Trial Registry: ACTRN12614000957695. Date registered: 8 September 2014.

## Background

Recovery-oriented practice involves facilitating a process of change through which individuals who have been diagnosed with mental illness are supported to reclaim their personal identity, live a self-directed life, and strive to reach their full potential [1, 2]. This can be seen as a paradigm shift in specialist mental health service delivery, from a focus on ameliorating symptoms to an approach that recognises people’s strengths, self-capacity and potential for personal recovery, even in the context of ongoing symptoms or disability [3, 4]. The history of the international recovery movement is longstanding and influenced by the consumer movement as well as emerging evidence that challenges more pessimistic assumptions about recovery from severe and persistent mental illness [5, 6]. Note that in this paper we will use the term consumer to refer to a person with a diagnosis of mental illness or who uses mental health services. The impact of this paradigm shift towards recovery can be identified in mental health policy, practice and law in all Australian states and territories, especially in the last 10 years [7], and is gradually transforming services.

### The development of a recovery orientation in mental health in Victoria

Since the concept of recovery first emerged from the consumer movement in the 1970s and 1980s, the reorientation of mental health policy and services toward recovery has gained increasing momentum in the Victorian mental health sector [8]. At the national level, recovery was first formally endorsed in the 2003–2008 Australian National Mental Health Plan [9]. Subsequent developments in the community-managed health sector accelerated the Australian recovery movement over the following decade, including the establishment of early intervention alternatives to inpatient treatment such as the sub-acute Prevention and Recovery Care (PARC) programs. In 2011, the Victorian Government commissioned a framework document supporting the development of evidence-based recovery-oriented mental health services with an emphasis on facilitating personal recovery and dismantling barriers to full participation in community life for people with experiences of mental illness [8]. This was followed in 2014 by the implementation of a new Mental Health Act in Victoria that established recovery as a fundamental guiding principle in the provision of mental health care. Recovery has thus emerged as a core feature of contemporary reform to mental health service planning and delivery at both the state and national level. Complementing these developments has been an increasing emphasis on the importance of “co-design” or “co-production” to ensure that consumers, families and carers are centrally involved in the design, development and delivery of mental health services [10, 11]. Despite these reforms, the mental health care system still has a long way to go in being responsive to the cultural and linguistic diversity of the Australian population [12]. Little is known about the effectiveness of mental health interventions across people of different cultural and linguistic groups and whether the contemporary emphasis on recovery orientated practice is having the presumed positive impacts on consumers.

### REFOCUS

The value and efficacy of system-wide transformation to focus on recovery is yet to be empirically established in Australia. In the UK, a staff training intervention (called REFOCUS) promoting personal recovery and enabling organizational change in specialist mental health services has been developed and trialled [13]. Based on a systematic review and narrative synthesis of existing literature on recovery, the REFOCUS team developed a conceptual framework of personal recovery, which identified five key recovery processes denoted by the acronym “CHIME”: Connectedness, Hope, Identity, Meaning, and Empowerment [14]. This conceptual framework informed the development of a team-based training intervention for community mental health teams in England that was designed to promote recovery through changes in staff and team skills, knowledge, behaviour, values and relationships with consumers [13]. In a large scale cluster randomized controlled trial (cRCT), the outcomes of usual care plus the REFOCUS intervention were compared with usual care only (control) in 27 community mental health teams delivering services to adult patients with psychotic disorders. The primary outcome, personal recovery as assessed using the Questionnaire about the Process of Recovery (QPR), did not differ between the REFOCUS intervention group and controls, although staff-rated functioning and unmet needs did improve in the intervention group [15]. The authors suggest that implementation was the central challenge, and when high-participating teams were compared with low-participating teams, higher participation was associated with higher staff-reported recovery-promotion behaviour and improved consumer-rated QPR. Challenges in implementing the intervention at the team level included variability in staff participation and adherence to recovery-oriented training procedures [16] along with the diluting effects of staff turnover. Participant attrition was higher than anticipated (26% vs 7%) resulting in a reduction in planned statistical power. A further proposed possible reason for the overall lack of difference between the intervention and control group on recovery outcomes is that the 12-month timeframe may have been of insufficient length for the intervention to take effect. On average, patient participants had been using mental health services for more than 15 years, suggesting the possibility of established staff-consumer relationships and entrenched ways of relating to services and problems that may take longer than 1 year to change [17].

### PULSAR

In the Principles Unite Local Services Assisting Recovery (PULSAR) Specialist Care trial, REFOCUS training materials and the research design have been adapted to enable the testing of the intervention in specialist mental health care services in Australia. The PULSAR staff training intervention aims to train community mental health staff in recovery-oriented practice, so as to embed recovery principles in mental health service delivery in the southern metropolitan region of Victoria, Australia. The PULSAR Specialist Care trial is part of the broader PULSAR research program focused on promoting recovery-oriented practices which also includes the Australian primary care sector [18]. The study components were co-designed with a consumer academic (VE), and the involvement of PULSAR Lived Experience Advisory Panel (LEAP) created for the project (see *Leadership structure* below) and facilitated by VE. This paper outlines the PULSAR Specialist Care study protocol. The protocol follows the Standard Protocol Items: Recommendations for Interventional Trials (SPIRIT) guidelines [19].

### Objectives

Using a mixed methods design, the primary objective of the PULSAR Specialist Care study is to evaluate whether adults accessing study cluster specialist mental health services where staff receive the recovery-oriented practice training intervention report superior recovery outcomes compared to adults accessing services where staff have not received the intervention. The following research questions will be addressed:From pre- to post-intervention, do consumers in intervention clusters report greater improvements in a) personal recovery b) health and well-being, and c) perceived need and satisfaction with services compared with consumers receiving care in control groups?From pre- to post-intervention, do ethnic minority consumers in intervention clusters report greater improvements on measures of personal recovery compared to ethnic minority consumers receiving care during control phases?

A nested qualitative sub-study involving consumers and staff will be conducted. For consumers, the research question that will be addressed is:How do consumers experience and view the support for their recovery in services where the PULSAR training has taken place?

For staff, the research questions to be considered are:What factors help and hinder working in a recovery-oriented manner, from the perspective of staff who have received the PULSAR training intervention?What experiences and dilemmas are encountered when implementing recovery-oriented practices within different parts of the Australia mental health service system, and what strategies are used to address the issues identified?

A nested process evaluation sub-study aims to examine quantitative and qualitative data including documents and processes related to training implementation and the uptake of new ways of working in order to articulate important explanatory variables relating to clusters that affected the rollout of the intervention and potentially influenced the study outcomes.

## Methods

### Overall design

The PULSAR Specialist Care project is one of two multisite two-step stepped-wedge cRCTs within the broader PULSAR research program [18]. The study design of the PULSAR Specialist Care project is a mixed methods design incorporating a two-step stepped-wedge cluster randomized controlled trial (cRCT) examining cross-sectional data from three phases, and nested qualitative and process evaluation sub-studies (see Fig. 1 and Table 1). Co-design with a consumer academic who is an author (VE) was a key design driver, and this co-design began early when the initial protocols were drafted for the application for funding.

**Fig. 1 Fig1:**
[figure not shown]
PULSAR Specialist Care study design and planned timeline Notes. Indicated at the *bottom* is the study year. The two-step cluster randomise control trial is shown: half the clusters receive the intervention in step 1 and the remaining clusters receive the intervention in step 2. For a summary of the study evaluations see Table 1

**Table 1 Tab1:** Evaluation plan for the PULSAR Specialist Care study

	Sub-study name	Evaluation design	Unit of analysis	Number	Number at each time point	Number in each cluster at each time point	Detectable differences		
							Primary outcome, QPR	Secondary outcome, WEMWBS	Secondary outcome, INSPIRE
cRCT (quantitative data)	Stream 1 (primary analysis)	cross-sectional cRCT (complete step-wedge)	Consumers (mail-out)	756	252 at baseline 252 at step 1 252 at step 2	18	6.34 (medium effect)	NA	NA
	Stream 2	pre- and post-intervention (incomplete step-wedge)	Consumers (interviews)	252 (stream 1 subset)	63 at baseline 126 at step 1 63 at step 2	9	7.68 (medium effect)	4.80 (medium effect)	7.72 (medium effect)
	Stream 3	longitudinal, (same participant, 12-mths apart pre- and post-intervention)	Consumers with diagnosis of psychosis (interviews)	88 (stream 2 subset)	44 at baseline & step 1 44 at step 1 & step 2	6–7	10.94 (medium-large effect)	6.84 (medium-large effect)	11.28 (medium-large effect)
Nested Qualitative study (qualitative data)			Consumers Staff	20–24 20–24	10–12 at step 1 10–12 at step 2	Nested sub-study examining qualitative data collected in study interviews and focus groups			
Nested Process evaluation (both quantitative & qualitative data)			Consumers & staff	The process evaluation assesses a specific set of qualitative, quantitative and documentary data relating to each cluster.					

Notes. The primary analysis examines the primary outcome– the Questionnaire about the Process of Recovery (QPR) - collected in the two-step stepped-wedge cluster randomized controlled trial (cRCT). A subset of consumers in the cRCT participate in study interviews where secondary outcomes measuring well-being, service satisfaction and health economic impact are collected In a yet another subset in the cRCT, longitudinal data are collected via interviews that are 12 months apart from consumers with a diagnosis of a psychotic disorder. Qualitative and process evaluation sub-studies are nested within the overarching cRCT and include information from consumers and staff.

A cluster randomized design was selected to minimize the threat of contamination between treatment and control groups, as the intervention is administered at the service (cluster) level [15, 20], these clusters being specialist mental health care services in Melbourne, Victoria (see Table 2). The stepped-wedge design was implemented for pragmatic and ethical reasons; in addition to allowing the intervention to be staggered across study clusters, the stepped design offers the ethical advantage of enabling all participating clusters to receive an intervention that is predicted to be beneficial [21]. A mixed method design was utilized for reasons including that the integration of quantitative and qualitative methods provides a richer dataset than can be gained with either approach alone [22, 23]. This in turn allows for a comprehensive and multifaceted evaluation of the project outcomes, as well as further explaining those outcomes and enhancing the project’s credibility. The latter is an important consideration in large-scale projects involving multiple stakeholders, as is the case with the PULSAR project [23]. There are additional benefits to using qualitative and quantitative methods at different stages in the intervention trial; for example, exploratory qualitative techniques were initially used to identify potential obstacles to implementing recovery-oriented practice in service settings and to inform the intervention design, while quantitative methods are used to evaluate the effectiveness of the training intervention. Furthermore, following the intervention trial, qualitative methods are being used to gain a more nuanced understanding of staff experiences of implementing recovery-oriented practices and consumer views of these practices across different settings within Victoria’s mental health service system.

**Table 2 Tab2:** Cluster sites and stratification factors

Cluster	Team/service	Organisation	Site	Strata	Team/service description
Cluster 1	Crisis assessment & treatment team	Monash Health	1	A	Crisis Assessment and Treatment Teams (CATTs) provide urgent assessment and short-term treatment to people in psychiatric crisis and play a key role in triaging admissions to hospital.
Cluster 2	Crisis assessment & treatment team	Monash Health	2	A	
Cluster 3	Mobile support and treatment service + Community Care Unit	Monash Health	3 4	B	Mobile Support and Treatment Teams (MSTs) provide intensive long-term support through assertive outreach to people with prolonged and severe mental illness with associated high levels of disability. Community Care Units (CCUs) provide medium to long-term residential rehabilitation in a home-like environment.
Cluster 4	Mobile support and treatment service + Community Care Unit	Monash Health	5 6	B	
Cluster 5	Community Mental Health Service	Monash Health	7	C	Community Mental Health Service (CMHS) provide non-urgent assessment, treatment, case management, and continuing care support to people living in the community over varying periods of time.
Cluster 6	Community Mental Health Service	Monash Health	8	C	
Cluster 7	Continuing Care	Monash Health	9	D	Continuing Care Teams (CCTs) provide non-urgent assessment, treatment, case management, and continuing care support to people living in the community over varying periods of time.
Cluster 8	Continuing Care	Monash Health	10	D	
Cluster 9	PARC – Adult + PARC – Extended	Mind Australia	11 12	E	PARC services (including youth, adult and extended PARCs) provide short-term residential support and treatment to assist in averting acute inpatient admission or facilitate earlier discharge.
Cluster 10	PARC – Youth	Mind Australia	13	E	
Cluster 11	PARC Ermha	Ermha	14	F	
Cluster 12	PARC Ermha	Ermha	15	F	
Cluster 13	Community outreach services	Mind Australia	16	G	Community Outreach Services provide a range of individualized psychosocial support and recovery services.
Cluster 14	Community outreach services site 1 Community outreach services site 2	Ermha	17 18	G	

Note. Clusters are stratified by the team/service type and composition: i.e. there are seven different strata

The PULSAR Specialist Care trial will take 4 years to complete, beginning in 2013 and concluding in 2017, see Fig. 1. The original study protocol (documented in the Australian New Zealand Clinical Trials Registry, or ANZCTR) was developed over a period of 18 months in consultation with Chief Investigators (CIs) and an advisory committee comprised of representatives from local specialist and community care organizations, consumers and family/carers, and experts in legal, cultural and educational aspects of mental health service delivery in Victoria. Although minor adaptations have been made to the original protocol, as outlined below, the over-arching two-step stepped-wedge cRCT design remains unchanged and the trial is on target to reach completion within the anticipated 4 year timeframe. All adaptations to the study protocol were considered by, and required the approval of, the appropriate Module Committee governing the relevant aspect of the project (see *Study leadership* section) along with the governing Human Research Ethics Committees.

The PULSAR training intervention is being delivered to 14 specialist mental health care clusters (see Table 2), with clusters randomized to receive the intervention 12 months apart, as shown in Fig. 1. To ensure that cluster types are balanced, stratified randomization was applied, for the strata see Table 2.

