### Sample size

The primary analysis examines QPR data from consumers in the cRCT (stream 1) and requires a total sample size of 756 consumers from 14 clusters over 3 years (see Table 1). This will be sufficient to detect a medium effect size representing a change in QPR score by 6.34, see Table 1. Secondary analyses that examine data from a subset of stream 1 consumers who participate in stream 2 of the cRCT, requires a total sample size of 252 consumers over the study period. This will be sufficient to detect medium effect sizes in the QPR and two secondary outcome measures (WEMWBS and INSPIRE), see Table 1. Additional secondary analyses to examine longitudinal data from a subset of stream 2 consumers who participate in stream 3 of the cRCT, requires a total sample size of 88 consumers over the study period. This will be sufficient to detect medium-large effect sizes in the QPR and WEMWBS and INSPIRE, see Table 1.

Sample size calculations were based on 14 clusters; intracluster correlation coefficient (ICC) of 0.05; significance level set at 0.05; power of 0.80; and available published [34, 36, 45] and unpublished (INSPIRE) data about distribution properties. All sample size calculations indicate the minimum number of participants we aim to recruit and were done using Stata statistical software *stepped-wedge* [46] Version 11, StataCorp. 2009.

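### The stream 2 detectable differences in Table 1 do not fit the planned 9 consumers per cluster per time point; they fit 18, and at 9 the power for them is about 60-62%

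*Protocol article*

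**What the plan says.** Table 1 (Methods, Overall design) describes stream 2 as a pre/post comparison in an incomplete stepped wedge. Its sample is "63 at baseline 126 at step 1 63 at step 2", which is 252 interviews with 9 in each cluster at each time point. The detectable differences in that row are "7.68 (medium effect") for QPR, 4.80 for WEMWBS and 7.72 for INSPIRE.

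The Sample size section relies on this row. It says of the 252 interviews: "This will be sufficient to detect medium effect sizes in the QPR and two secondary outcome measures (WEMWBS and INSPIRE), see Table 1". The inputs it states for all streams are: "Sample size calculations were based on 14 clusters; intracluster correlation coefficient (ICC) of 0.05", "significance level set at 0.05" and power 0.80. It gives no SDs and refers to published data and, for INSPIRE, unpublished data.

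The other two rows of Table 1 serve as checks:

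- Stream 1 is a complete wedge with 18 per cluster per time point and a QPR difference of 6.34.
- Stream 3 has 6-7 per cluster, with 10.94 for QPR, 6.84 for WEMWBS and "11.28 (medium-large effect") for INSPIRE.

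**The concern.** Stream 2 has half of stream 1's number per cluster and time point, and it lacks the T0 and T2 comparisons between the two randomized groups. Its printed QPR difference is nevertheless only 21% larger than stream 1's (7.68/6.34 = 1.211). The step from stream 2 to stream 3 is also too large for a fall from 9 to 6 or 7 per cell.

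Table 1 gives no stream 1 figure for WEMWBS or INSPIRE, because both are collected only at interview. Stream 2 is therefore the main source of evidence on the two named secondary outcomes. If its row overstates the precision, a null secondary result could be read as excluding a difference of 0.48 SD that the sample was not large enough to detect with the stated power.

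**Working it through.** **Inputs.** From the Sample size section: 14 clusters, ICC ρ = 0.05, alpha 0.05, power 0.80. Sidedness is not stated; two-sided reproduces the table, so the multiplier is 1.9600 + 0.8416 = 2.8016. From the Abstract: half the clusters train in each year, so 7 + 7. From Main analysis plan for cRCT: intervention and time are fixed effects and cluster is random (stated for the primary model). Let m be the number per cluster per time point and s = (1 − ρ)/m. All results are in SD units.

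**Formulas**

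- *Complete wedge (stream 1).* The T1 difference between the two groups of clusters is adjusted for their T0 and T2 differences: Var = (2/7)[ρ + s − 2ρ²/(2ρ + s)].
- *Incomplete wedge (streams 2 and 3).* There are four group-by-period cells and four mean parameters (three periods and one effect). T0 and T2 each contain only one group, so they add nothing to the effect estimate, and only the T1 contrast remains: Var = (2/7)(ρ + s). Re-interviewing the same people does not change this.

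Detectable difference = 2.8016 × √Var × SD.

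**Reproducing the rows that fit**

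- Stream 1, m = 18: s = 0.05278. Var = (2/7)(0.10278 − 0.005/0.15278) = 0.02001. Detectable 0.3963 SD. The printed 6.34 implies SD 6.34/0.3963 = 16.0.
- Stream 3, m = 6: Var = (2/7)(0.05 + 0.15833) = 0.05952. Detectable 0.6835 SD. The printed 10.94 implies SD 16.0 and 6.84 implies SD 10.0.

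**Stream 2**

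| m | Var | Detectable (SD) | QPR, SD 16 | WEMWBS, SD 10 |
|---|---|---|---|---|
| 9 (planned) | (2/7)(0.15556) = 0.04444 | 0.5906 | 9.45 | 5.91 |
| 18 | (2/7)(0.10278) = 0.02937 | 0.4801 | 7.68 | 4.80 |
| Printed | | | 7.68 | 4.80 |

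At m = 9 the printed values would need SDs of 13.0 (QPR) and 8.1 (WEMWBS), which do not agree with the other rows.

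**Check that does not need the SD.** Ratios between rows cancel a common SD.

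- Stream 3 / stream 2, printed: 10.94/7.68 = 1.424 and 6.84/4.80 = 1.425. Theory for 6 against 18: √(0.20833/0.10278) = 1.424. For 6 against 9: √(0.20833/0.15556) = 1.157.
- Stream 2 / stream 1, printed: 1.211. Theory with stream 2 at 18: √(0.10278/0.07005) = 1.211. At 9: √(0.15556/0.07005) = 1.490.
- A different ICC shared by streams 2 and 3 does not help. For 6 against 9 the ratio is largest at ICC 0, where it is √(9/6) = 1.225, still short of 1.424.

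**Other settings tried for stream 2 at m = 9, SD 16.** One-sided alpha gives 8.39, power 0.70 gives 8.38, and a complete wedge gives 8.68. None gives 7.68.

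**Power at the printed values, m = 9.** The standard error is √0.04444 = 0.2108 SD. For QPR and WEMWBS: Φ(0.48/0.2108 − 1.96) = 0.624. Holding 7.68 at 80% power would take 18 × (7 + 14 + 7) = 504 interviews.

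**INSPIRE.** 7.72/0.4801 = 16.1 at m = 18, while 11.28/0.6835 = 16.5 at m = 6. The two cells do not share one SD (11.28/7.72 = 1.461, against 1.424-1.425 for the other outcomes). At m = 9 the detectable difference is 0.5906 × 16.08 = 9.50 to 0.5906 × 16.5 = 9.74, and power at 7.72 is 62% to 60%.

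**The case against.** The strongest objection is that the 62% is conditional. The SDs are not in the protocol and are backed out of the same table. The fixed time effect is specified for the primary QPR model, whereas the sentence on secondary outcomes speaks only of comparing intervention with control periods. If stream 2 were analysed as a plain pre/post contrast without time, 9 per cell would detect 0.344 SD (5.50 for QPR) and power at 0.48 SD would be about 97%. That stands as a caveat. It does not explain the table: without time, the three QPR rows would need SDs of 6.34/0.2073 = 30.6, 7.68/0.3440 = 22.3 and 10.94/0.4213 = 26.0. Such an analysis would also confuse the effect with any change over calendar time.

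It is also fair that the prose in Sample size claims only a medium effect. At 0.59 SD, stream 2 would still lie below the 0.68 SD that Table 1 calls medium-large, so the label can stand. It is the printed differences that do not.

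A reader might go further and infer that stream 3 is also unattainable. Its 88 pairs are 70% of the 126 pre-training interviews (63 + 63), and the Background says of the earlier REFOCUS trial that "Participant attrition was higher than anticipated (26% vs 7"%). The documents do not support that step. Table 1 gives the 88 as people interviewed at both time points, the Sample size section calls all its numbers minimums, and the 26% belongs to a different trial.

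Nor is the INSPIRE mismatch a proven error. It is about 2.6%, its source data are unpublished, and stream 3 is a narrower population in which some people skip INSPIRE, so the two SDs may differ for a reason.

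**Conclusion.** The point holds for the stream 2 row. The printed QPR and WEMWBS differences are inconsistent with 9 per cluster per time point and agree to two decimals with 18. That 18 was actually entered, perhaps as 252/14, is an inference. It is a strong one, because two outcomes and two comparisons between rows lead to it, but the protocol does not say so.

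At the planned size the detectable differences are about 23% larger than printed (9.45/7.68 = 1.23), and power at the printed values is about 60-62% instead of 80%. This assumes fixed period effects, a cluster random intercept, ICC 0.05, two-sided alpha, and the inferred SDs of 16.0 (QPR), 10.0 (WEMWBS) and 16.1-16.5 (INSPIRE).

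The error is confined to secondary analyses. It would be wrong to infer that the trial's primary comparison is underpowered: stream 1's 6.34 reproduces exactly.

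**What to change.** Restate the stream 2 row of Table 1, on which the Sample size section relies, in one of two ways:

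- give detectable differences at 80% power of about 9.45 (QPR), 5.91 (WEMWBS) and 9.5-9.7 (INSPIRE); or
- keep 7.68, 4.80 and 7.72 and state power of about 62% for them (60-62% for INSPIRE).

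In either case, state the SDs used and that the calculation includes time effects. Confirm from the original sample size output which number per cluster per time point was entered. At the same time, reconcile the INSPIRE cells: either use one SD for 7.72 and 11.28, or say why the two streams differ. The stream 1 and stream 3 QPR and WEMWBS figures need no change.

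The cost is a text correction. Recruitment targets, allocation and analysis stay as they are; only the stated sensitivity of the secondary analyses becomes less favourable.
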